### Healthy Controls

Healthy adults (aged ≥18 years) will be age- and sex-matched with the participants with EDS and G-HSD. Individuals will be excluded from the study if they meet the following criteria:

Diagnosis of a respiratory, cardiovascular, or musculoskeletal condition that may contribute to exercise limitationPresence of cardiac pacemaker or implantable defibrillatorInsufficient English fluency to provide informed consent or inability to follow study protocolsSelf-reported pregnancyActive smoker (cigarettes or marijuana)

### Assessments

At T_0_, the participants with hEDS and G-HSD will undergo pulmonary function tests (PFTs), cardiopulmonary exercise test (CPET) with fNIRS on the PFC, PROMs, and diaphragm ultrasound. The same assessments will be performed for healthy controls. Please refer to Table 1 for a detailed list of T_0_ measurements. At 4 weeks, respiratory muscle endurance assessment will be repeated for the participants with hEDS and G-HSD. All T_0_ assessments, including PFTs, CPET, PROMs, and respiratory muscle endurance assessment, will be repeated at 8 weeks for the participants with hEDS and G-HSD.

The following tests will be used to assess the primary and secondary outcome measures in the PFT laboratory at Toronto General Hospital.

### Respiratory Parameters

#### Assessment Using PFTs

##### Spirometry and Lung Volumes

Forced expiratory volume in 1 second, forced vital capacity, total lung capacity, and lung volumes (tidal volume, inspiratory capacity, expiratory reserve, and residual volumes) will be evaluated in accordance with the American Thoracic Society guidelines before CPET [40].

##### Oscillometry

This will be performed before other PFTs according to the European Respiratory Society Guidelines, as previously described [41,42]. Oscillometry provides detailed information regarding respiratory mechanics by measuring respiratory impedance, a complex sum of respiratory resistance, and reactance [43]. This technique uses sound waves to capture disturbances in airway resistance and can be a more sensitive marker of peripheral airway obstruction than spirometry [44,45]. Because it is performed during normal breathing, oscillometry is independent of effort and is not influenced by respiratory muscle strength. We will follow the quality assurance and control guidelines developed by our group using the tremoflo device (Thorasys) [46].

##### Respiratory Muscle Strength

MIP and maximal expiratory pressure will be evaluated using the American Thoracic Society standards. These measures will be repeated 3 times, and the highest value (cm H_2_O) that is 10% within the lower measures will be used [47,48].

##### Respiratory Muscle Endurance

The threshold loading device (Threshold IMT trainer [Philips]) [49] will be used to evaluate respiratory muscle endurance. We will assess the time that can be sustained at respiratory endurance at 30% of MIP obtained as part of the T_0_ measures after a brief familiarization session with the loading device. The maximum endurance that the threshold loading device can reach is 41 cm H_2_O. The endurance assessment will be repeated within 5 minutes if the participant stops the protocol early (<1 minute) because of severe coughing or lack of familiarity with the loading device. The maximum endurance that participants will be asked to perform is 15 minutes. Oxygen saturation will be concurrently monitored with pulse oximetry during the assessment.

##### Diaphragm Ultrasound

While the participant is in semirecumbent position, the research coordinator will place an ultrasound probe perpendicular to the chest wall in the 8th or 9th intercostal space between the anterior and midaxillary lines using a 5-13 MHz transducer (GE Logiq e Laptop Ultrasound System [GE Medical Systems]) [50]. Bright-mode ultrasound will be used to visualize the diaphragm, and motion-mode ultrasound will be used to assess the amplitude of the cranio-caudal diaphragmatic excursion during quiet and deep breathing. Diaphragm thickness will be measured as the distance between the leading edges of the diaphragmatic pleura and peritoneum at resting end expiration and after peak inspiration. Thickening fraction, an established marker of diaphragm strength, will be calculated as follows: ([diaphragm thickness at end expiration–diaphragm thickness at peak inspiration] divided by diaphragm thickness at end expiation) × 100 [50].

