#### Assessment Using CPET

##### Overview

Symptom-limited CPET will be performed on a cycle ergometer (Elema), with exhaled gas measurements captured breath by breath, as routinely applied in our PFT laboratory. Testing will start with 2 minutes of complete rest on the bike, followed by unloaded pedaling for 2 minutes, and then exercise intensity will be increased by 10 to 20 W per minute using a ramp protocol. Blood pressure, 12-lead electrocardiogram, and peripheral oxygen saturation will be continuously monitored. Inspiratory capacity, tidal volumes, and respiratory rate will be measured throughout the exercise to assess for any dynamic hyperinflation and ventilatory reserve. Heart rate (HR) response, peak aerobic capacity, oxygen pulse (measure of cardiac stroke volume), and minute ventilation (product of tidal volume and respiratory rate) will be collected throughout the exercise and up to 2 minutes after test completion with unloaded pedaling, with percent predicted values reported. HR recovery (difference between peak HR and HR 1 minute after exercise) and the chronotropic response index ([peak HR – resting HR × 100] / [220 – age] – [resting HR]) will be collected as a measure of autonomic function [51-53]. Chronotropic incompetence is the inability to decrease HR after exercise or the inability to reach 80% of the maximal age-predicted HR because of abnormal sympathetic activation [51]. Symptom intensity for breathing and leg discomfort with exercise will be measured at rest and every 3 minutes throughout the exercise using the Borg dyspnea [54] and leg fatigue scales [55]. The reasons for exercise cessation will be ascertained from the participants (ie, dyspnea, leg fatigue, both, or other). To ensure participant safety before CPET, 12-lead electrocardiograms will be performed for both the participants with hEDS or G-HSD and healthy controls.

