**Secondary outcomes**						
	**Pulmonary function**					
		Spirometry and lung volumes	FEV1^b^ (L), FVC^c^ (L), TLC^d^ (L), RV/TLC^e^ (%)		Baseline (T_0_) and 8 weeks (T_2_)	
		Oscillometry	Oscillometry: respiratory impedance, reactance, and resistance		Baseline (T_0_) and 8 weeks (T_2_)	
		Respiratory muscle endurance time	Time (seconds) using the Philips Threshold trainer at 30% of baseline MIP		Baseline (T_0_), 4 weeks (T_1_), and 8 weeks (T_2_)	
		Diaphragm structure and function	Diaphragm thickness and thickening fraction		Baseline (T_0_) and 8 weeks (T_2_)	

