	**Cardiopulmonary exercise parameters**					
		Aerobic and anaerobic capacity	Peak aerobic capacity, anaerobic threshold, breathing reserve, and cycling power output		Baseline (T_0_) and 8 weeks (T_2_)	
		HR^j^ response and chronotropic response	HR recovery (HR at 1 minute after CPET^k^ – HR at the end of CPET) and chronotropic response index adjusted for age ([peak HR – resting HR × 100] / [220 – age] – [resting HR])		Baseline (T_0_) and 8 weeks (T_2_)	
	Neural activity during exercise (prefrontal cortex)		Oxyhemoglobin and total hemoglobin concentration changes		Baseline (T_0_) and 8 weeks (T_2_)	

^a^MIP: maximal inspiratory pressure.

^b^FEV1: forced expiratory volume in 1 second.

^c^FVC: forced vital capacity.

^d^TLC: total lung capacity.

^e^RV/TLC: residual volume/total lung capacity ratio.

^f^PROM: patient-reported outcome measure.

^g^MRC: Medical Research Council.

^h^HRQL: health-related quality of life.

^i^SF-36: Short Form-36.

^j^HR: heart rate.

^k^CPET: cardiopulmonary exercise test.

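### Two secondary-outcome formulas are wrong as printed: the diaphragm thickening fraction has its numerator reversed, and the chronotropic response index is bracketed so that it mostly tracks resting heart rate

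*Protocol article*

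**What the plan says.** **Thickening fraction (Diaphragm Ultrasound).** The numerator is "diaphragm thickness at end expiration–diaphragm thickness at peak inspiration", and the rest of the formula reads "divided by diaphragm thickness at end expiation) × 100". The same sentence introduces the measure with "Thickening fraction, an established marker of diaphragm strength". Table 3 lists "Diaphragm thickness and thickening fraction" as a secondary outcome at baseline and 8 weeks. The Proposed Data Analyses section also names the thickening fraction as a possible determinant of peak Borg dyspnea.

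**Chronotropic response index (Assessment Using CPET, Overview).** The formula is "peak HR – resting HR × 100] / [220 – age] – [resting HR", with an opening bracket before the first term and a closing one after the last. It is offered as a measure of autonomic function. Table 3 repeats it: "chronotropic response index adjusted for age ([peak HR – resting HR × 100] / [220 – age] – [resting HR".

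**Heart rate recovery.** The CPET overview has "HR recovery (difference between peak HR and HR 1 minute after exercise", with no order of subtraction. Table 3 gives heart rate at 1 minute after the test minus "HR at the end of CPET".

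**The concern.** The article prints these formulas itself, so they are not details left to an analysis plan. No other section corrects the first two.

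The thickening fraction as printed contradicts its name and its stated meaning, because a diaphragm that thickens more gets a lower score. Someone who computes it as printed and reads it as strength would report an improvement as a deterioration. The same reader would also get the wrong sign for its association with dyspnea.

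The chronotropic index has a worse fault. Read with ordinary operator precedence, the printed expression is not a reversed or rescaled version of the intended index. It is a different quantity, with almost no information on how far heart rate rises during exercise.

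**Working it through.** The plan gives no figure to reproduce, so each formula was evaluated as printed and then with the terms reordered or grouped. The documents give no thickness or heart rate values. All inputs below are assumed for illustration.

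**1. Thickening fraction.** Let E be thickness at end expiration and I thickness at peak inspiration.

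- Printed: 100 × (E - I) / E
- Reordered: 100 × (I - E) / E

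| E (mm) | I (mm) | Printed | Reordered |
|---|---|---|---|
| 2.0 | 3.0 | -50% | +50% |
| 1.8 | 3.6 | -100% | +100% |
| 2.0 | 5.0 | -150% | +150% |

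The printed value is exactly the negative of the reordered one. Mean changes, group differences and the regression coefficient for this predictor therefore change sign and keep their size. A simulated comparison of 17 against 17 confirms this: t = 2.608 and t = -2.608, with p = 0.0137 both ways.

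**2. Chronotropic response index.** Let P be peak heart rate, R resting heart rate and A age.

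- Printed: (P - 100R) / (220 - A) - R
- Both terms grouped: 100 × (P - R) / ((220 - A) - R)

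For P = 170, R = 70, A = 30:

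- Printed: (170 - 7000) / 190 - 70 = -35.9 - 70 = -105.9
- Grouped: 100 × 100 / (190 - 70) = 83.3

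Further cases at age 35:

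| R | P | Printed | Grouped |
|---|---|---|---|
| 80 | 130 | -122.5 | 47.6 |
| 80 | 170 | -122.3 | 85.7 |
| 80 | 185 | -122.2 | 100.0 |
| 60 | 170 | -91.5 | 88.0 |
| 100 | 170 | -153.1 | 82.4 |

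At age 35, one extra beat of peak heart rate moves the printed value by 1/185 = 0.005. One extra beat of resting heart rate moves it by -(100/185 + 1) = -1.54. With R = 80, one extra beat of peak heart rate moves the grouped index by 100/105 = 0.95.

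A simulation assumed age 35 (SD 10), rest 80 (SD 10) and peak 165 (SD 15). The printed value correlated -0.99 with resting heart rate, 0.00 with peak heart rate and 0.03 with the grouped index.

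Grouping only one side does not rescue the formula. For A = 35, R = 80, P = 170, grouping only the numerator gives -31.4 and grouping only the denominator gives -74.6.

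**3. Heart rate recovery.** With 170 at peak and 145 at 1 minute, Table 3 gives 145 - 170 = -25. The CPET overview, if read in word order, gives 170 - 145 = +25, but it states no sign. The two places also differ in reference point: peak in one, end of test in the other. The magnitudes agree when the peak occurs at the end of the test.

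**The case against.** The strongest reply is that these are typesetting slips. The chronotropic formula looks like a stacked fraction flattened onto one line, and Table 3 may simply copy the text. Values near -106 would be noticed at once, and the name of the thickening fraction makes its direction plain. All this is plausible, and it limits what can be claimed: the documents do not show that the trial computes either measure as printed. It does not remove the point, because the printed formulas are the only ones the article gives, and an analyst following them would get wrong values.

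It is also fair that the article never describes the index as a percentage of heart rate reserve. The finding does not need that description. The same paragraph explains chronotropic incompetence partly as failing to reach 80% of age-predicted maximal heart rate, so a measure that barely responds to peak heart rate cannot serve the stated purpose.

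A reader might infer that heart rate recovery is a third wrong outcome, defined with opposite signs in two places. The text does not support that. The CPET overview gives an unsigned difference, which a signed formula does not contradict, and Table 3 gives a usable change score in which a fall is negative. What remains is an unsettled convention and reference point.

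**Conclusion.** Two secondary-outcome formulas are wrong as printed and should be corrected. For the thickening fraction the error is one of sign only: direction reverses, while magnitudes and two-sided p values stand. For the chronotropic index the error removes the content: in the assumed cases at age 35 and rest 80, raising peak heart rate from 130 to 185 moves the printed value by 0.3 and the grouped index by 52.4. The numerical sizes depend on the assumed inputs. The sign reversal holds for any diaphragm that thickens on inspiration, and the weak dependence on peak heart rate follows from the printed brackets.

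Two wider readings are tempting and not supported. One is that effect directions flip across all these outcomes; that is shown only for the thickening fraction. Neither the chronotropic index nor heart rate recovery is among the listed determinants of dyspnea. The other is that data already collected are wrong. The Results section reports only enrollment and completion counts, and the documents show neither stored derived values nor the code used to derive them. The primary pilot outcome (MIP), the feasibility criteria and the sample size are unaffected.

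**What to change.** - **Thickening fraction:** print 100 × (thickness at peak inspiration - thickness at end expiration) / thickness at end expiration.
- **Chronotropic response index:** print 100 × (peak HR - resting HR) / ((220 - age) - resting HR), in both the CPET overview and Table 3.
- **Heart rate recovery:** state one signed definition and one reference point (peak or end of test) in both places. Either sign convention is workable if it is fixed and reported.
- **Check:** confirm which formulas are in use for participants already assessed, and recompute only if the printed ones were used. As of January 2023 the Results section reports 4 + 4 = 8 trial completers, 5 further trial participants enrolled and 11 healthy controls completed, so the check is small.

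The cost is a short correction to the text and one table, plus that check. No new data and no change to design or sample size are needed.

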#### Assessment Using CPET

##### Overview

Symptom-limited CPET will be performed on a cycle ergometer (Elema), with exhaled gas measurements captured breath by breath, as routinely applied in our PFT laboratory. Testing will start with 2 minutes of complete rest on the bike, followed by unloaded pedaling for 2 minutes, and then exercise intensity will be increased by 10 to 20 W per minute using a ramp protocol. Blood pressure, 12-lead electrocardiogram, and peripheral oxygen saturation will be continuously monitored. Inspiratory capacity, tidal volumes, and respiratory rate will be measured throughout the exercise to assess for any dynamic hyperinflation and ventilatory reserve. Heart rate (HR) response, peak aerobic capacity, oxygen pulse (measure of cardiac stroke volume), and minute ventilation (product of tidal volume and respiratory rate) will be collected throughout the exercise and up to 2 minutes after test completion with unloaded pedaling, with percent predicted values reported. HR recovery (difference between peak HR and HR 1 minute after exercise) and the chronotropic response index ([peak HR – resting HR × 100] / [220 – age] – [resting HR]) will be collected as a measure of autonomic function [51-53]. Chronotropic incompetence is the inability to decrease HR after exercise or the inability to reach 80% of the maximal age-predicted HR because of abnormal sympathetic activation [51]. Symptom intensity for breathing and leg discomfort with exercise will be measured at rest and every 3 minutes throughout the exercise using the Borg dyspnea [54] and leg fatigue scales [55]. The reasons for exercise cessation will be ascertained from the participants (ie, dyspnea, leg fatigue, both, or other). To ensure participant safety before CPET, 12-lead electrocardiograms will be performed for both the participants with hEDS or G-HSD and healthy controls.

##### Assessment Using fNIRS

fNIRS is a noninvasive method that uses continuous optical topography to evaluate increases in oxygenated hemoglobin levels, an indicator of PFC activity that has been suggested to be associated with dyspnea [56-58]. The change in oxyhemoglobin and deoxyhemoglobin will be monitored using the Artinis fNIRS device (Artinis Medical Systems) [59], which will be secured over the participant’s forehead, with the center of each sensor pad vertically aligned with the iris. Light intensity data at 2 wavelengths (730 and 850 nm) will be obtained during CPET from the left and right sides of medial PFC and dorsolateral PFC using a cognitive optical brain imaging software at a sampling frequency of 4 Hz. Detector gain settings will be adjusted for light intensity, and filters will be applied to attenuate the physiological artifacts of respiration and pulse.

#### Assessment Using PROMs

##### Dyspnea

The Medical Research Council (MRC) dyspnea scale [60], Borg dyspnea scale [54], and 18-item qualitative dyspnea descriptors will be used [61]. This will allow us to evaluate the quantitative and qualitative changes in respiratory symptoms.

*MRC dyspnea scale*: the MRC dyspnea scale (1-5) will be used to assess the effect of breathlessness on daily activities at T_0_ [60]. It allows patients to indicate the extent to which breathlessness limits their daily functioning [60].*Borg dyspnea scale*: the highest score on a 10-point Borg scale at the beginning and end of CPET will be measured. The participants will also be asked to indicate their daily Borg dyspnea score before and after their IMT practice in their participant logs [62].*Qualitative dyspnea descriptors:* the qualitative dyspnea descriptors scale comprises a list of 18 dyspnea descriptors. Qualitative descriptors of dyspnea will be ascertained at T_0_ and at the end of CPET [61].

##### Exercise Behaviors and Physical Activity

Exercise behaviors will be measured using the 3-item Godin Leisure-Time Exercise Questionnaire—Leisure Score Index, which is a reliable and validated measure for this population [63]. This index assesses the frequency of mild, moderate, and strenuous bouts of leisure physical activity performed for at least 15 minutes over the past week. In addition, physical activity will be measured using a tracking device (Fitbit), which will record daily steps and active minutes for the study participants with hEDS or G-HSD [64,65].

##### Measurement of HRQL

The Short Form-36 Health Survey (version 1.0) will be used to assess generic HRQL [66]. It comprises 8 health domains that contribute to 2 physical and mental component scores (ranging from 0 to 100), with higher scores representing better HRQL. A 5-point change in the physical component scores or mental component scores is considered clinically significant [66].

##### Depression, Anxiety, and Stress

The Depression, Anxiety, and Stress scale has 21 items to assess mood (depression, anxiety, and stress) and has been administered to patients with hEDS [8]. It has acceptable to excellent internal consistency, and normative data are available [67].

### Anthropometric Measures

Standard anthropometric measures will be captured for all the participants. Height, weight, waist circumference, and BMI information will be collected for the participants with hEDS or G-HSD from the electronic patient charts. The same measures will be collected for healthy controls during the T_0_ assessments.

### Clinical Assessments

We will abstract standard GEAR program measures from the medical charts for all the participants with hEDS or G-HSD: 6-minute walk distance, lower extremity function (5-repetition sit-to-stand test), hand-grip strength, Bristol questionnaire, and Godin Leisure-Time Exercise scale. The Beighton score [68], Charlson comorbidity index [69], and medications such as opioids that can impact dyspnea will be abstracted from chart review.

### Sociodemographic Parameters

We will abstract information on demographics such as age, ethnicity, sex, employment status, education level, and lifestyle factors (eg, smoking status) from the medical charts for the participants with hEDS or G-HSD. Demographic data will be collected from healthy controls via a demographic survey.

### Randomization

After T_0_ assessments, the participants will be randomly allocated to the intervention or usual care group using a 1:1 ratio stratified by hEDS or G-HSD. The allocation of the participants to their groups will be randomized (blocks of 2 to 4) using shuffled, opaque envelopes by a biostatistician. The study participants and the research team and coordinator supervising the IMT will be aware of the group assignments.

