#### Intervention Group (IMT)

The participants in the intervention group will receive an individual and personalized prescription for an IMT program for 8 weeks. This IMT program will use the POWERbreathe K5 IMT device in the participants’ home environment combined with the standard-of-care rehabilitation as part of the GEAR program, as described earlier. A research coordinator will facilitate these training sessions and monitor the participants via the web for the first 3 sessions in the first week and once a week from weeks 2 to 8. Over 8 weeks, 2 daily IMT sessions of 30 breaths (<5 min/session) will be performed for 5 days per week, starting with 20% of the participants’ T_0_ MIP up to a maximum of 60%. This protocol was developed based on the previous literature on IMT applied in lung transplant candidates at our center [70-72]. The total workload per session (product of inspiratory muscle force and inhaled volume expressed in Joules) will be abstracted from the IMT device. Additional variables abstracted from the device will include inspiratory muscle load (cm H_2_O), mean power per breath (W), and mean volume per breath (Liters).

The participants will be asked to record their resting and post-IMT Borg dyspnea scores for 5 days of the week (2 sessions per day), along with any side effects for each session. The median Borg dyspnea score for the previous week will be reviewed by the research coordinator, and IMT intensity will be increased by 5% to 10% of the T_0_ MIP if the median weekly Borg dyspnea score is <7 (very severe breathlessness with IMT) [54].

The participants will be asked to maintain IMT diaries to assess adherence. They will receive instructions and feedback on how to optimize their home training efforts based on direct observation of their IMT with the POWERbreathe K5 device and review of IMT workload from the device. They will have the possibility to schedule additional sessions with the study team during the week, if further support is needed.

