#### Data Management and Quality Assurance

Our research team is trained in the measurement protocols and has expertise in performing physical assessments and PROMs in individuals with respiratory conditions. The research team has critically appraised the peer-review comments from the 2020 GoodHope Ehlers-Danlos Syndrome foundation grant (Multimedia Appendix 1) and has incorporated them into the study protocol. Most of the study assessments will be conducted at the PFT laboratory of Toronto General Hospital by experienced respiratory technicians. All equipment (ultrasound, fNIRS, and oscillometry) has been applied in the laboratory setting previously. In addition, our research team has expertise in conducting web-based assessments in the participants’ home environment, including IMT, given the COVID-19 environment.

The research coordinator will guide the participants through each step of the study process. Standard operating procedures will be generated for each step related to data collection, data entry, and data handling. The research coordinator will ensure accuracy by periodically auditing the data in our research database. Although the research coordinator will attempt to have the participants complete the entirety of the assessments and questionnaires, if there are unanswered questions or missing data, the data will not be imputed, and analysis will be performed on the available data.

The current institutional and national research ethics guidelines will be followed to ensure data privacy, security, and protection. Participant data will only be accessible by the research study team, and participants will be assigned a random participant ID, which will be linked to all the data. All the study data will be securely stored on a password-protected server. In the event of inappropriate data breaches, the following actions will be undertaken: (1) prevent further breach of information and attempt to retrieve breached information and (2) notify the institutional research ethics board immediately. Further action might be taken according to the recommendations from the research ethics board. Modifications to the study protocol will be approved by the research ethics board before implementation, communicated to funding agencies, and outlined in future publications.

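### The diaphragm ultrasound, a secondary outcome, is assigned to the coordinator role that supervises IMT and knows the allocation, and no masking of it is described

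*Protocol article*

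**What the plan says.** Four places in the protocol article bear on this.

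- Randomization: "The study participants and the research team and coordinator supervising the IMT will be aware of the group assignments".
- Intervention Group (IMT): "A research coordinator will facilitate these training sessions and monitor the participants via the web". This contact covers the first three sessions and then one session a week to week 8. The coordinator also reviews the weekly Borg scores on which the training load is progressed.
- Diaphragm Ultrasound: "the research coordinator will place an ultrasound probe perpendicular to the chest wall". The section describes how thickness is measured and how the thickening fraction is calculated. It does not say who takes the measurements from the image.
- Table 3 lists "Diaphragm thickness and thickening fraction" as a secondary outcome at baseline and 8 weeks.

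Two statements under Data Management and Quality Assurance give context. On the coordinator: "The research coordinator will guide the participants through each step of the study process". On the laboratory: "Most of the study assessments will be conducted at the PFT laboratory of Toronto General Hospital by experienced respiratory technicians".

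**The concern.** Without a sham device, participants will know their arm, and the article says so openly. That makes it more important who measures the outcomes. For the ultrasound, the plan names a role that has coached one arm for eight weeks, has had no comparable contact with the other, and knows the allocation.

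The measurement leaves room for judgment: where the probe sits, which of two intercostal spaces is used, which frame represents end expiration or peak inspiration, and where the edges of a thin structure are placed. An operator who expects the trained diaphragm to thicken could lean that way without intending to. At stake is the trial's evidence on diaphragm structure and function, which the Introduction names as a gap left by the previous IMT trial in hEDS and which the Discussion presents as part of the mechanistic yield.

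**Working it through.** No figure in the plan is disputed. The check sets the passages side by side and then illustrates sensitivity.

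**1. Who knows the arm.** Randomization names the participants, and the research team and coordinator supervising IMT.

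**2. Who supervises IMT.** A research coordinator, per Intervention Group (IMT).

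**3. Who scans the diaphragm.** The research coordinator, per Diaphragm Ultrasound. That this is the same person is an inference from the role. It is a reasonable one: no second coordinator is mentioned, and Data Management and Quality Assurance describes a single coordinator role across the whole study.

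**4. When the exposure arises.** Allocation follows the baseline assessments, so baseline scans are acquired before anyone knows the arm. Week-8 scans are acquired after. An error related to arm therefore falls on the second value only and passes straight into the change score. Baseline images are exposed too if they are measured later.

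**5. Whether masking is described.** It is not described for this outcome, at acquisition or at measurement.

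**6. Sensitivity of the thickening fraction (TF).** The article gives no thickness values. *Assume* 2.0 mm at end expiration, 3.0 mm at peak inspiration and a reading error of 0.1 mm. The article's formula subtracts peak from end-expiratory thickness and so returns the negative of these values; magnitudes are shown.

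- No error: TF = (3.0 − 2.0)/2.0 = 50.0%
- End-expiratory reading 0.1 mm low: (3.0 − 1.9)/1.9 = 57.9%
- Peak reading 0.1 mm high: (3.1 − 2.0)/2.0 = 55.0%
- Both readings 0.1 mm low: (2.9 − 1.9)/1.9 = 52.6%

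The same error moves TF by 2.6 to 7.9 percentage points, depending on where it falls. This shows that the ratio is sensitive to small reading differences. It does not estimate the bias in this trial.

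**7. How much could still benefit.** The Results section reports 4 + 4 = 8 randomized participants completed as of January 2023, so 34 − 8 = 26 of the planned 34 had not then completed. If images have been stored, the earlier ones can also be re-measured under code.

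**The case against.** The strongest reply is that this is a 34-participant open-label feasibility pilot, that it discloses who is aware, and that the overlap touches one secondary outcome among many. It is also fair that the article names who places the probe but not who measures thickness, and that standard operating procedures are promised for each data-collection step. This limits the weight of the point. It does not remove it, because the assignment of the scan to an aware role is stated in the text and is not an omission.

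A reader might go further and infer that the primary pilot outcome is measured unmasked. The documents do not support that. MIP is a best effort ("These measures will be repeated 3 times, and the highest value (cm H_2_O) that is 10% within the lower measures will be used"), so encouragement could matter. But most laboratory tests are done by respiratory technicians, who are not separately named in the Randomization statement, and nothing says they are told the arm. MIP testing also follows a professional society's standards.

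Two numerical arguments for the stronger reading should also be set aside:

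- The 10% rule for MIP efforts, applied to the assumed mean of 51 cm H2O, gives 5.1, close to the planned difference of 10 − 5 = 5 cm H2O. But the rule is a repeatability criterion within one session and the 5 is a difference between group means. Their similarity says nothing about bias.
- With no true effect, SD 3.5, 14 per arm (17 × 0.8 = 13.6, rounded up) and a two-sided 5% *t* test, assumed between-arm biases of 1, 2 and 3 cm H2O would give rejection rates of about 11%, 31% and 59%. This shows why tester masking is worth having, but nothing in the article indicates a bias of any such size.

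Nor is assessor masking the only protection available, since standardized test procedures also help.

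**Conclusion.** The point holds for the ultrasound. As written, the plan assigns the week-8 diaphragm scan to the coordinator role that supervises IMT and knows the allocation, and it describes no masking. The conclusion assumes that the coordinator named in the different sections is one role, which the text supports without stating outright. The size of any bias cannot be derived from the documents; the shift of 2.6 to 7.9 points is an illustration on assumed thicknesses and an assumed error.

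For MIP, the article is compatible with technicians who do not know the arm, so there is no demonstrated fault, only a safeguard worth writing down. The whole is an inexpensive improvement to a pilot and not a flaw that undermines its primary result.

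**What to change.** **Main change.** Store every ultrasound clip under a code that hides participant, arm and visit, with the key held by someone other than the reader. Have an existing team member measure thickness and thickening fraction in one batch after week-8 collection, and say so in the Diaphragm Ultrasound section.

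**Minor addition.** State that the technicians who test week-8 MIP are not told the arm, that participants are asked not to disclose it, and that the IMT device is handed back after testing. Table 2 places device collection and laboratory testing in the same week-8 row, so the order matters.

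**Limitation to state.** Masked reading does not remove bias in image acquisition, because probe position and breathing instructions stay with the aware coordinator. Masking the tester does not remove the influence of unblinded participants' own effort on MIP. The Limitations section mentions neither.

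**Cost.** Some file coding and key-keeping, and ultrasound values that arrive later. No additional staff are needed if an existing team member reads the images. Technician masking will sometimes be broken, and those occasions can be recorded.
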